**Functional status outcomes**													
Health status-short form 12	12		X				X		X	X	X	X	PQO
Work and social activity scale	5		X				X		X	X	X	X	PQO
Quality of life enjoyment satisfaction questionnaire	15		X				X		X	X	X	X	PQO

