### Primary and secondary outcome measures

The primary outcome measurement was improvement of depression severity after 8 weeks, as measured through change in HAM-D total scores from pre- to post-treatment, treatment response (scores ≥ 50% decrease from baseline) and remission (post-treatment scores ≤ 7). Length of treatment efficacy, a secondary outcome, was assessed up to 1 year after baseline using HAM-D scores, response and remission rates by measuring rate of depression relapse using the semi-structured Longitudinal Interval Follow-up Evaluation (LIFE) [35]. The participant-rated 16-item Quick Inventory of Depressive Symptomatology (QIDS) [36] was used as a secondary measurement to assess change in depressive severity, response (scores ≥ 50% decrease from baseline) and remission (scores ≤ 5) during the same treatment and follow-up time period.

Functional status and quality of life were additional secondary outcomes measured using the SF-12 Health Survey [37,38], the Work and Social Adjustment Scale (WSAS) [39], [40] and the Quality of Life, Enjoyment, and Satisfaction Questionnaire (Q-LES-SQ) [41].

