### Planned analytic approach

The primary outcome measure of the HAM-D will be compared between participants randomized to the MBCT + TAU and the HEP + TAU groups using a mixed-effects statistical model [58,59]. Mean levels of severity, and response and remission rates at week 8 and bivariate measures will be compared between treatment conditions using logistic regression models with generalized estimating equations to correct for interdependence resulting from group membership. The secondary outcome measures of the QIDS-SR and CGI will be compared using the same methodology but replacing the HAM-D with the QIDS-SR and CGI severity measures. We will also assess relapse occurrence in both arms using the LIFE interview at weeks 24, 36 and 52.

The efficacy of MBCT + TAU versus HEP + TAU on functional status as a secondary outcome will be assessed using similar models to the methods used to test the reduction in HAM-D_17_ scores. For each of the four scales, scores at week 8 will be compared between randomized conditions using a mixed-effects statistical model, which will include effects for randomized condition, therapy group and baseline disability score. The test of the estimated parameter for treatment condition will be a direct test of this hypothesis. Mediating effects of the relationship of treatment assignment with outcome will be tested using a series of linear regression models. Putative mediators, enhanced mindfulness (FFMQ), enhanced self-compassion (SCS), diminished rumination (RRS) and decreased experiential avoidance (AAQ) will be assessed at weeks 4, 8, 24, 36, and 52. We will also assess persistence of treatment changes in depression (HAM-D, QIDS-SR, CGI), functional status (SF-12, WSAS, Q-LES-Q-SF), mindfulness (FFMQ), rumination (RRS), self-compassion (SCS) and avoidance (AAQ) at weeks 24, 36 and 52 by analyses parallel to those outlined for testing Hypotheses 1 and 2 using data from the weeks 24, 36, and Week 52. Mixed-effects and logistic regression models using a generalized estimating equation (GEE) will allow direct testing of these effects. Moderating factors (e.g. age of depression onset, prior poor treatment outcomes, co-morbid psychiatric diagnoses and other socio-demographics) associated with TRD will also be included in the model.

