Additional secondary analyses will test for effects of time. These models will also include indicator variables of any additional treatments (e.g. HEP participants’ crossing over to take MBCT outside of the research), medication changes after the end of acute treatment before the 24, 36 and 52-week follow-ups and also whether or not patients began new psychotherapeutic interventions after treatment or continued formal meditation practices.

Based on the extent and nature of missing data (outcomes, predictors, baseline, and items from scales), we will use one of several strategies for data analysis. We anticipate that the majority of missing data will result from participant attrition. In this case, we will know the randomization assignment and have data from some, but not all, of the planned assessments. Our primary approach to dealing with this monotone missing data pattern will be a pattern-mixture modeling approach [60]. We may also be missing some data on predictors, even in the absence of participant attrition. Our primary method for dealing with missing predictor values will be multiple imputation using a regression modeling approach [60]. This method is superior to simpler methods such as using group means for missing data. In order to limit attrition, we will provide an incentive in the form of an assessment payment schedule to increase motivation to complete all assessments.

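### The stated test of the functional-status and quality-of-life scales does not use the week-4 scores, and the article does not say whether the pattern-mixture analysis does

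*Protocol article*

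**What the plan says.** The section on primary and secondary outcome measures gives these scales their rank: "Functional status and quality of life were additional secondary outcomes measured using the SF-12 Health Survey", followed by the work and social scale and the quality-of-life questionnaire.

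Under the planned analytic approach, efficacy on functional status "will be assessed using similar models to the methods used to test the reduction in HAM-D" scores. The next sentence is more specific: "scores at week 8 will be compared between randomized conditions using a mixed-effects statistical model, which will include effects for randomized condition, therapy group". The list of effects ends with "therapy group and baseline disability score". The test is then fixed: "The test of the estimated parameter for treatment condition will be a direct test of this hypothesis". No visit or arm-by-visit term is listed.

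In Table 4 the functional-status rows (SF-12, "Work and social activity scale" and the quality-of-life questionnaire) are marked at weeks 0, 4, 8, 24, 36 and 52. There is therefore one treated measurement before week 8. In the same part of the analysis section, week 4 is named for the mediators but not for the functional scales. Persistence is to be examined "by analyses parallel to those outlined for testing Hypotheses 1 and 2" with data from weeks 24, 36 and 52. Effects of time are left to additional secondary analyses.

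On attrition, the article expects most missing data to come from dropout, where "we will know the randomization assignment and have data from some, but not all, of the planned assessments". Its primary approach to this monotone pattern is pattern-mixture modelling. The outcome model for that analysis is not described.

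**The concern.** A model whose only outcome is the week-8 score takes no information from someone who gave a week-4 score and then left. The article expects about 20% attrition and acknowledges that partial data will exist, yet the test it specifies for its functional hypothesis has no slot for them.

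Two things are at stake. The first is precision: week 4 is probably the best single predictor of a missing week-8 score. The second is protection against selective loss. Participants know their allocation, and the safety plan itself anticipates withdrawals linked to features of each intervention, so dropout that differs by arm is plausible. If it follows week-4 status, a comparison of observed week-8 scores adjusted only for baseline carries part of that selection into the treatment estimate.

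**Working it through.** **Inputs from the article.** Total sample 124, taken as 62 per arm on an assumed 1:1 allocation; attrition about 20%; functional scales at weeks 0, 4 and 8. The article gives no figure for the functional analysis itself. Its sample size is consistent with these inputs: 50 per arm evaluable gives 100/0.8 = 125, against 124 stated.

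**Assumed inputs.** The correlations among weeks 0, 4 and 8 and the dropout mechanism. The article gives neither, so ranges are shown. Clustering by therapy group is ignored.

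**Step 1: precision.** Let r be the partial correlation of weeks 4 and 8 given baseline:

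r = (r48 − r04·r08) / √[(1 − r04²)(1 − r08²)]

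If n4 and n8 are the proportions observed at weeks 4 and 8, and dropout is random, the variance of the week-8 contrast using week 4, relative to week 8 alone, is

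ratio = 1 − r²(1 − n8/n4), with n8 = 0.80.

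If half of the dropouts have a week-4 score, n4 = 0.90 and 1 − n8/n4 = 0.111. If all do, n4 = 1 and the term is 0.20.

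| r04, r08, r48 | r | r² | ratio, half | ratio, all |
|---|---|---|---|---|
| 0.50, 0.40, 0.60 | 0.504 | 0.254 | 0.972 | 0.949 |
| 0.55, 0.45, 0.70 | 0.607 | 0.368 | 0.959 | 0.926 |
| 0.60, 0.50, 0.70 | 0.577 | 0.333 | 0.963 | 0.933 |
| 0.60, 0.50, 0.80 | 0.722 | 0.521 | 0.942 | 0.896 |

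The reduction in variance runs from 2.8% to 10.4%, equivalent to about 3% to 12% more patients (1/0.972 and 1/0.896). A simulation with 124 participants, the third row's correlations, random dropout and all week-4 scores present gave standard errors of 0.176 and 0.169 SD, a variance ratio of 0.92. With complete data there is essentially no gain.

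**Step 2: bias of the week-8-only comparison.** The simulation used true effects of 0.25 SD at week 4 and 0.50 SD at week 8, correlations 0.60, 0.50 and 0.70, 18% to 20% loss, all after week 4, and a log-odds slope of 0.8 per SD where dropout depends on a score.

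| Dropout depends on | Week 8 only | Weeks 4 and 8 |
|---|---|---|
| nothing (random) | 0.00 | 0.00 |
| baseline | 0.00 | 0.00 |
| week 4, alike in both arms | −0.01 | 0.00 |
| week 4, one arm only | 0.05 | 0.00 |
| week 4, opposite directions by arm | 0.11 | 0.00 |

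The sign depends on which arm loses its poorer scorers.

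**Hand check of the last two rows.** With dropout probability p = 1/(1 + exp(1.7 + 0.8z)) for a standard normal week-4 score z, mean dropout is 0.181 and the mean of p(1 − p) is 0.135. Those who stay have a week-4 mean shifted by 0.8 × 0.135/0.819 = 0.132 SD. The part of week 8 tied to week 4 beyond baseline is 0.70 − 0.60 × 0.50 = 0.40. The bias is about 0.132 × 0.40 = 0.053 SD from one arm, and twice that, 0.106, when the arms move in opposite directions. This agrees with the simulation.

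**Step 3: sensitivity.** A second simulation used 62 per arm, correlations 0.55, 0.45 and 0.70, and a steeper slope of 1 per SD. Bias was 0.04 to 0.09 SD when half of the dropouts left before week 4 at random, and 0.08 to 0.16 SD when all left after it. The repeated-measures estimate stayed within 0.01 SD of the truth. Both simulations analyse observed week-8 scores without a pattern-mixture step.

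**The case against.** The strongest reply is that the article already names a method for attrition. A monotone pattern is defined across visits, and pattern-mixture models exist to specify the unobserved outcome within each dropout pattern, often conditional on earlier scores. A reader might infer that the week-4 data are thrown away, or that a pattern-mixture model would have nothing to model for someone without a week-8 score. Neither follows. The article is silent on whether week-4 scores enter that analysis, and a missing final score is the case such models are built for. The bias figures above therefore describe the stated test before any pattern-mixture step, not the whole plan.

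Three further replies have weight. The listed effects are what the model will include and need not be exhaustive, and the models are said to be similar to those for the HAM-D, so a condensed article may leave detail to the analysis plan. The article also does not establish that the follow-up analyses are separate one-visit fits. And a baseline-adjusted comparison at the end of treatment is a legitimate analysis of a secondary outcome.

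A reader might also suppose that week-4 rows would be pooled, so that the condition parameter averages two visits. The text specifies the week-8 score, and no stated analysis does this.

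What remains is that the one functional test the article spells out has no term through which week 4 could contribute, and that time effects appear only in additional secondary analyses.

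**Conclusion.** The point holds as a modest, inexpensive improvement to the analysis of secondary outcomes, not as an error that invalidates the comparison. The stated week-8 test does not use the week-4 scores, and their role in the pattern-mixture analysis is unstated.

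Under the assumed correlations and 20% attrition, including week 4 would lower the variance of the week-8 contrast by about 3% to 10%. The protection against bias is conditional: roughly 0.05 to 0.11 SD where dropout follows week-4 status differently by arm, more or less than that with the slope and the timing of loss, and at most about 0.01 SD otherwise. A reader might take the week-8 model to be biased whenever people drop out; the calculations do not support that. Nor do they cover dropout that depends on unobserved scores, where the repeated-measures model is not guaranteed to be unbiased either.

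**What to change.** For the SF-12, the work and social scale and the quality-of-life questionnaire, fit one repeated-measures mixed model per scale to the post-baseline visits, using at least weeks 4 and 8. Include arm, visit, arm-by-visit, the scale's own baseline score, baseline-by-visit and a therapy-group effect, with unstructured within-person covariance. State that the functional hypothesis is tested by the arm contrast at week 8 from this model, which keeps the article's end-of-treatment target. Build the pattern-mixture analysis on the same longitudinal model and say how week-4 scores enter it.

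The cost is a change of wording, a little programming and a few more covariance parameters. No new data, visits or patients are needed.

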### Description of interventions

The two treatments, MBCT and HEP consisted of 8 weekly classes, each lasting 2.25 hours. In addition to attending weekly classes, participants in both groups were encouraged to complete 45 minutes of homework six days per week for the duration of the 8-week treatments. Both interventions were conducted in a group format with 6–12 participants per group and were led by two facilitators extensively trained in their respective techniques.

MBCT is a manualized treatment that combines training in mindfulness meditation with elements of cognitive therapy. For the purpose of this study, MBCT was adapted from the original manual developed by Segal et al. [11] with modifications for TRD, the details of which are published elsewhere [13]. These modifications are believed to promote enhanced emotional regulation specific to TRD through increasing an individual’s nonjudgmental awareness of their present moment experience [13]. MBCT teaches skills that encourage patients to disengage from habitual (“automatic”) dysfunctional cognitive routines, in particular depression-related ruminative thought patterns, as a way to reduce current symptoms, future risk of relapse and recurrence [16]. Through guided meditation practices and activities, participants are taught to develop more present-focused, non-judgmental awareness of their thoughts and feelings instead of focusing on the content of them [11,14,15,18]. It is theorized that the same cognitive processes known to make individuals prone to depression relapse are also active in perpetuating depression once it is established [12] and are a primary driver of TRD.

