### Summary

In summary, the results of this trial will address whether MBCT, previously shown to be effective for relapse prevention, may be an effective augmentation therapy for patients with TRD in active depressive episodes. In addition, this is the first RCT to compare whether MBCT is more effective in reducing depression, rates of relapse and disability when augmented by medications (TAU) than an active comparator condition; thereby isolating the elements of MBCT that might be most salient. In particular, the study will highlight whether mindfulness or other features of the interventions play important roles in the outcomes. In addition, the study will shed light on which MBCT factors play mediating roles in producing its effects. National self-report surveys have found complementary and alternative techniques such as mindfulness, are being used by 41% to 54% [63] of individuals with depression, indicating that there is substantial public demand for mindfulness-based treatment interventions. Consequently we believe the results of this study will have significant applications for depression care by informing providers about targeted, population-based non-pharmacological interventions strategies that may also be appealing to TRD patients.

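### The mediation tests are specified as linear regressions with no therapy-group adjustment, although the same section corrects other outcomes for group membership; run as written, the treatment-to-mediator test rejects too often

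*Protocol article*

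**What the plan says.** All the models concerned are in the protocol article, section Planned analytic approach.

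- **Response and remission at week 8** are compared "using logistic regression models with generalized estimating equations to correct for interdependence resulting from group membership".
- **Functional-status scales at week 8** are compared "using a mixed-effects statistical model, which will include effects for randomized condition, therapy group and baseline disability score".
- **Mediation**: "Mediating effects of the relationship of treatment assignment with outcome will be tested using a series of linear regression models". The putative mediators are mindfulness (FFMQ), self-compassion (SCS), rumination (RRS) and experiential avoidance (AAQ). No group term, random effect or GEE is named.
- **Persistence at weeks 24, 36 and 52**, which covers the same four mediator scales: "Mixed-effects and logistic regression models using a generalized estimating equation (GEE) will allow direct testing of these effects".

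On delivery, the section Description of interventions says: "Both interventions were conducted in a group format with 6–12 participants per group". The section Randomization and baseline assessment makes the patient the unit of randomization. Each therapy group therefore lies wholly within one arm.

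Examining mediators is part of the secondary objectives (Research objectives), and the Summary promises that "the study will shed light on which MBCT factors play mediating roles in producing its effects".

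**The concern.** The plan accepts that members of one therapy group are not independent and acts on this for several outcomes. For mediation it then names a different class of model and no such correction. Because groups are nested in arm, variation between groups adds directly to the variance of the arm contrast. A regression that treats participants as independent leaves that part out, so chance differences between a few groups can be read as an effect of MBCT on the mediator.

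The treatment-to-mediator step also matters by itself. The Discussion promises to report whether the mediators improve more under MBCT than under HEP over the 8 weeks. The persistence models cover the mediators only at weeks 24 to 52. For the week-8 mediator contrast, the linear regressions are the only model that the article names.

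At stake are false statements about mechanism and intervals for indirect effects that are too narrow.

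**Working it through.** **Inputs**

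- From the article: groups of 6 to 12 (midpoint 9); 124 participants; about 20% attrition; up to about 50 per condition before allowing for attrition.
- Assumed, because the article does not state them: two-sided 5% level; ICC from 0.01 to 0.10; the rule for declaring mediation.

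**Step 1. The plan's own figure.** 50 / 0.8 = 62.5 per arm, or 125 in total, against 124 stated. In reverse, 124 × 0.8 / 2 = 49.6 analysed per arm. The sample size is consistent with its own attrition. The article states no error rate for mediation, so there is none to reproduce.

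**Step 2. Error of the treatment-to-mediator test when groups are ignored.** With design effect DEFF = 1 + (m − 1) × ICC, the true two-sided level is 2 × [1 − Φ(1.96 / √DEFF)].

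Example, m = 9 and ICC = 0.05: DEFF = 1 + 8 × 0.05 = 1.40; 1.96 / √1.40 = 1.656; level = 0.098.

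| ICC | m = 6 | m = 9 | m = 12 |
|---|---|---|---|
| 0.01 | 0.056 | 0.059 | 0.063 |
| 0.02 | 0.062 | 0.069 | 0.076 |
| 0.05 | 0.080 | 0.098 | 0.115 |
| 0.10 | 0.110 | 0.144 | 0.176 |

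If each group loses 20% of its members (m = 4.8, 7.2, 9.6), the levels are 0.054, 0.057 and 0.060 at ICC 0.01; 0.072, 0.087 and 0.101 at ICC 0.05; and 0.095, 0.124 and 0.151 at ICC 0.10.

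**Step 3. ICC at which the level doubles to 10%.** Set 1.96 / √DEFF = 1.645, so DEFF = 1.42 and ICC = 0.42 / (m − 1). This gives 0.084 for m = 6, 0.053 for m = 9 and 0.038 for m = 12.

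**Step 4. Effect on a full mediation claim.** Simulation with about 50 analysed per arm, in 10 groups of 5, 6 groups of 8 or 5 groups of 10 per arm, and 3,000 trials per cell. Both steps were fitted by regression without a group term. Mediation was declared when both steps were significant (the joint test).

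| Situation | ICC 0 | ICC 0.02 | ICC 0.05 | ICC 0.10 |
|---|---|---|---|---|
| Mediator related to outcome (0.5), not moved by treatment | 0.045–0.052 | 0.059–0.066 | 0.069–0.103 | 0.095–0.163 |
| Both paths null | at most 0.004 | at most 0.005 | at most 0.006 | at most 0.019 |
| Treatment moves mediator, mediator unrelated to outcome (group effects correlated 0.7) | 0.050–0.056 | 0.049–0.057 | 0.060–0.064 | 0.087–0.098 |

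The Sobel test is more conservative. In the first situation it runs at 0.030–0.033 at ICC 0 and 0.066–0.125 at ICC 0.10.

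**Step 5. Check on one possible remedy.** A percentile bootstrap that resamples whole groups within arm was simulated for the treatment-to-mediator contrast with no true effect (about 50 per arm, 3,000 trials per cell, ICC 0 to 0.10). Its error was 8–9% with 10 groups per arm, 8–10.5% with 7 and 11–12% with 5. The moment estimate of the group variance was zero or negative in about 27–43% of trials at ICC 0.02 to 0.05.

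**The case against.** **The article may simply be brief.** It says only linear regression and does not exclude a cluster-robust variance or a group term. It is a condensed account, and such detail for a secondary analysis is often left to the statistical analysis plan. Part of this stands: that the regressions treat participants as independent is an inference. But the section distinguishes its model classes and names the group correction where it intends one. For mediation it names a method, and that method, followed as written, gives too small a standard error. This is more than missing detail.

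**The size depends on assumptions.** This stands. A reader might infer that the error is at least twice nominal. The article does not support that: it gives no ICC, and at ICC 0.01 to 0.02 the level is only 5.6% to 7.6%. The inflation also falls mainly on one step, and the joint test is below nominal when both paths are null. The relevant case is still plausible, because the Discussion anticipates that these scales may be associated with outcome.

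**Other stronger readings also fail.** A reader might attribute the whole risk of a false finding among four mediators to clustering. In a simulation with four mediators intercorrelated at 0.5 and 9 per group, the chance of at least one false finding was 35% at ICC 0.10, but already 15% at ICC 0. That part is multiplicity. Nor does the article say that each group had its own facilitators; it says that groups had two trained facilitators. Facilitators shared across groups would remove one source of between-group variation.

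**The consequences are limited.** This also stands. The mediators are to be examined as a secondary objective, and at weeks 24 to 52 the mediator scales are covered by mixed or GEE models.

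**Conclusion.** The point holds in a bounded form. The mediation regressions carry no stated therapy-group adjustment, unlike the response, remission and functional-status models in the same section. Run as written, the treatment-to-mediator test is anti-conservative: about 6% to 18% instead of 5% for groups of 6 to 12 and an assumed ICC of 0.01 to 0.10, or about 5% to 15% if groups shrink by 20%. Doubling is a mid-range possibility, not a minimum.

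For a joint mediation claim, the damage is greatest when the mediator tracks depression but is not moved by treatment (about 6% to 16% over ICC 0.02 to 0.10). It is absent when both paths are null. These figures rest on a two-sided 5% level and, for the joint claim, on an assumed decision rule.

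The primary HAM-D comparison has its own model and is not touched. The change should be made, but it does not bear on the trial's main conclusion.

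**What to change.** Replace the linear regressions for mediation with linear mixed models for both steps: treatment to mediator, and mediator to outcome given treatment. In each model:

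- include a therapy-group effect, as already planned for the functional scales. Make it random, since fixed effects for groups nested in arm would absorb the arm contrast;
- include the baseline value of the mediator or outcome;
- use degrees of freedom based on the number of groups, and keep them when the group variance is estimated at zero. Step 5 suggests that this will be common, and otherwise the model falls back to the uncorrected regression.

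Form the interval for the indirect effect by Monte Carlo from these estimates. Do not use a percentile bootstrap of whole groups, which is itself anti-conservative with about 5 to 10 groups per arm.

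If a cluster correction was intended all along, one sentence saying so, with these details, settles the matter. The cost is a sentence in the plan and a little programming, with no new data. The downside is somewhat wider intervals and less apparent power for the mediation tests.
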